**Fig. 1 Fig1:**
[figure not shown]
Trial diagram

Randomization was stratified by tumor location (cervical *V* thoracic) and tumor stage (II *V* III *V* IV). Written informed consent will be obtained from all patients before participation in this trial. All participating medical centers are well-experienced in radiotherapy and chemotherapy delivery.

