### Assessments during the treatment phase

The outcomes of physical examinations, vital signs, routine complete blood count, blood biochemistry, and radiotherapy-related pulmonary and esophageal toxicity will be recorded weekly during the dCCRT period, according to CTCAE (version 4.0). Changes in esophageal wall thickness and lymph node size (if needed) will be evaluated through contrast-enhanced CT of the neck, thorax, and abdomen. Changes in the esophageal tract will be assessed through contrast-enhanced CT of the upper gastrointestinal tract. The residual primary tumor will be evaluated through upper endoscopy followed by biopsy. Local tumors, locoregional lymph nodes, and distant metastases will be assessed through PET–CT. After 2–6 weeks of dCCRT, patients without disease progression will be randomized at a 1:1 ratio to arm A or B by a central randomization center; moreover, patients demonstrating disease progression will be excluded from the study.

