### Statistical analysis

Data analyses will be performed according to the intention-to-treat principle in all randomized patients. Between-group comparisons will be performed using chi-squared and Fisher’s exact test for categorical parameters and Student’s *t* test for normally distributed continuous variables or the Mann–Whitney *U* test or analysis of variance for nonnormally distributed continuous variables. Survival rates will be calculated using the Kaplan-Meier method, and comparisons between the groups will be performed using the log-rank test. The difference will be considered statistically significant at a *P* value of <0.05.

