## Discussion

Numerous trials have reported that compared with radiotherapy alone, dCCRT can significantly reduce treatment failure and prolong survival in patients with esophageal cancer [4–6, 14–16]. However, a majority of these trials have primarily included populations from Western countries, where esophageal adenocarcinoma is more prevalent than ESCC. In contrast, ESCC is the predominant histological type of esophageal cancer in China [2]. Therefore, exploring alternative treatment approaches specifically targeting ESCC is warranted.

Consolidation chemotherapy is defined as the prolongation of chemotherapy duration by the administration of additional drugs at the end of a defined number of initial chemotherapy cycles, after the achievement of maximum tumor response, in individual patients [17]. According to the RTOG 85-01 trial, the most adopted dCCRT scheme includes two cycles of consolidation chemotherapy after dCCRT [5]. However, the specific role and rationale for incorporating consolidation chemotherapy remain undefined; nevertheless, incorporating consolidation chemotherapy may reduce the likelihood of distant metastases and ultimately improve OS. Thus far, only a few retrospective studies have focused on consolidation chemotherapy. For instance, Chen et al. and Wu et al. have demonstrated that consolidation chemotherapy does not yield significant improvements in disease control or PFS in patients with ESCC. In contrast, Adenis et al. suggested that patients who undergo consolidation chemotherapy tend to have prolonged OS [11–13]. Furthermore, Wang et al. compared the potential survival advantages of consolidation chemotherapy and dCCRT alone in patients diagnosed as having unresectable esophageal cancer; the authors revealed a short-term survival benefit and a reduced likelihood of distant metastasis [18]. Similarly, Lin et al. and Xia et al. observed that consolidation chemotherapy is strongly associated with prolonged OS in ESCC patients undergoing dCCRT [19, 20]. However, the results observed across the aforementioned studies have been heterogeneous; therefore, additional prospective randomized controlled trials validating the benefits of consolidation chemotherapy in patients with ESCC are needed urgently.

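### Response after dCCRT, which the trial already assesses, enters neither the stratification nor the stated survival comparison: the test is not biased, but precision is lost and a response-dependent effect could be hidden in one pooled verdict

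*Protocol article*

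**What the plan says.** All places are in the protocol article.

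- **Who is randomised** (Assessments during the treatment phase): after dCCRT, "patients without disease progression will be randomized at a 1:1 ratio to arm A or B". Patients who have progressed are excluded.
- **What is measured** (same section): "The residual primary tumor will be evaluated through upper endoscopy followed by biopsy". Also: "Local tumors, locoregional lymph nodes, and distant metastases will be assessed through PET–CT". The only stated use of these results is to exclude progressors. The section does not date the work-up relative to randomisation.
- **Stratification** (text with Fig. 1): "Randomization was stratified by tumor location", cervical or thoracic, and by stage II, III or IV. The only staging that the article describes, under Inclusion criteria, is pretreatment staging.
- **Analysis** (Statistical analysis): "Data analyses will be performed according to the intention-to-treat principle in all randomized patients". For survival, "comparisons between the groups will be performed using the log-rank test". No response term is named.
- **Margin** (Sample size considerations): 15%, given beside 2-year OS rates of about 60% in Arm A and 48%–65% in Arm B. I read it as 15 percentage points of 2-year OS in the whole randomised population.

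**The concern.** By the time of randomisation, patients have had 33 fractions at five per week (33/5 = 6.6 weeks) and two cycles of chemotherapy. Their prognosis then plausibly depends on what the treatment achieved as well as on where they started. The design balances on starting characteristics only and does not use the later information, although the assessments that produce it are already planned.

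Two things are at stake. The first is precision: variation in OS that response explains stays in the error term. The second is interpretation. Arm B omits chemotherapy, and the non-inferiority verdict averages over patients with no detectable tumour and patients with residual tumour. If omission were harmless in one group and harmful in the other, the average could pass.

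**Working it through.** **The plan's own figure.** The total of 600 is not reproduced from the stated non-inferiority inputs. With 60% in both arms, a 15-point margin, one-sided 2.5%, 90% power and 5% dropout, the total is 474. With 80% power it is 354. That is a separate matter. Here 600 is taken as given, so 300 × 0.95 = 285 evaluable per arm.

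**Assumptions.** The article gives neither a response rate nor OS by response. For step 1, assume 50% complete response, Arm A 2-year OS of 60%, and a residual-versus-complete hazard ratio (HR) of 2 or 3. Step 2 varies the response share from 30% to 70%.

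**Step 1: precision.** Let s be 2-year OS in complete responders, so that OS with residual tumour is s^HR. Solve 0.5·s + 0.5·s^HR = 0.60.

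| HR | Complete | Residual | Gap | Share of variance = 0.25 × gap² / 0.24 |
|---|---|---|---|---|
| 2 | 70.4% | 49.6% | 20.8 points | 0.25 × 0.208² / 0.24 = 4.5% |
| 3 | 76.0% | 44.0% | 32.1 points | 0.25 × 0.321² / 0.24 = 10.7% |

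This is the variance that adjustment can remove when the arms are equal. The standardised estimate is

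Δ = w·[S_B(complete) − S_A(complete)] + (1 − w)·[S_B(residual) − S_A(residual)],

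where w is the share of complete responders in both arms combined. I simulated it with 285 per arm and 2-year status known for everyone:

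- True loss exactly 15 points: non-inferiority is declared in about 2.5% of trials, as for the unadjusted difference.
- Variance of the 2-year difference: about 5–12% lower across the scenarios.
- Power with equal arms: about 95% unadjusted, 96–97% standardised.
- Power at a true 5-point loss: about 67% unadjusted, 70–73% standardised.

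**Step 2: what pooling can hide.** Suppose Arm B loses nothing in complete responders and 15 points in patients with residual tumour. With complete-response share c, the pooled loss is L = 15(1 − c) points. The probability of declaring non-inferiority is Φ((0.15 − L)/SE − 1.96), with SE = √[(0.24 + p_B(1 − p_B))/285] and p_B = 0.60 − L.

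| c | L | p_B | SE | P(non-inferiority) |
|---|---|---|---|---|
| 30% | 10.5 points | 49.5% | 0.0415 | 19% |
| 50% | 7.5 points | 52.5% | 0.0414 | 44% |
| 70% | 4.5 points | 55.5% | 0.0413 | 72% |

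These declarations are correct for the pooled question, because L is below 15 points each time. They simply say nothing about the residual-tumour group.

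**Step 3: what a contrast by response could show.** With c = 50% there are about 142 patients per arm in each group. Using the overall binomial variance, the 95% half-width is 1.96 × √(0.48/142) = 11.4 points. That is informative but too wide to carry its own non-inferiority claim, so the contrast can only be supportive.

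**The case against.** The strongest reply is that the trial asks one coherent question, the average effect in all non-progressors, and that randomisation answers it without bias. Covariate adjustment and subgroups are also commonly left to a statistical analysis plan, which is not shown. Both points stand. The absence of such analyses from a condensed article does not show that they are unplanned. The stratification list, however, is explicit and belongs to the design. The stated comparison is an unadjusted one, and a better one is available from data already collected.

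Three stronger readings are tempting, and the documents do not support them.

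- **That ignoring response inflates false non-inferiority.** In simulation with a within-response HR of ln(0.45)/ln(0.60) = 1.563, an unadjusted Cox analysis declares non-inferiority in 4.7% to 9.0% of trials. But the protocol sets no hazard-ratio margin. Under the step 1 assumptions, that HR gives a true 2-year loss of only 14.4 points (HR 2) or 13.6 points (HR 3), both inside the 15-point margin. At an exact 15-point loss the unadjusted 2-year difference has a rejection rate of 2.4% to 2.7%. The shift in the hazard ratio is non-collapsibility, a change in the quantity estimated.
- **That chance imbalance in response is mistaken for a treatment effect.** An imbalance of ±8 points, with an assumed 30-point survival gap, moves the difference by 0.08 × 30 = ±2.4 points. This is already part of the ordinary 95% half-width of 1.96 × √(0.48/300) = ±7.8 points.
- **That only complete responders receive consolidation as the article defines it.** The Discussion's definition reads "after the achievement of maximum tumor response, in individual patients". Maximum response in an individual need not be complete, so a patient with residual tumour at best response meets it.

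**Conclusion.** The point holds as one of efficiency and interpretability, not validity. Response after dCCRT is assessed, but it is in neither the stratification nor the stated survival comparison. Under the assumptions above, using it would cut the variance of the 2-year OS difference by about 5–12%. Power would rise by one to two points with equal arms and by three to six points at a true 5-point loss, with type I error unchanged. A margin-sized loss confined to patients with residual tumour could coexist with a pooled non-inferiority finding in roughly 19% to 72% of trials, depending on the response share.

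All of these sizes rest on assumed response rates and prognostic strength, and the masking figures also rest on an assumed treatment effect by response. None comes from the documents. It is also inferred, not stated, that the response work-up is complete by randomisation. The exclusion of progressors at that moment implies that some disease assessment exists.

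**What to change.** 1. Record response at randomisation (complete versus residual, from the endoscopy, biopsy and PET–CT already planned) as a baseline variable. State that it is assessed before allocation, and how a missing or equivocal work-up is classed. For patients already randomised, use only assessments dated before randomisation.
2. Unless the statistical analysis plan already does so, adjust the primary OS comparison in all randomised patients for response, location and stage. Keep the 15-point margin on the marginal 2-year OS difference, for example with a response-standardised Kaplan–Meier difference. Do not carry the margin over to a conditional hazard ratio. Location, stage and response make 2 × 3 × 2 = 12 cells, so if some are sparse, standardise from a main-effects model instead of cell by cell.
3. Pre-specify the Arm B versus Arm A contrast by response as supportive, with confidence intervals and no separate non-inferiority claim.
4. Optionally, add response as a stratification factor for patients not yet randomised. The strata go from 6 to 12. Adjustment gives most of the benefit without this.

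The cost is one more field, a fixed date for the response work-up and slightly more analysis. No new procedure and no change to treatment is needed. Because the trial is open-label and 200 patients had been recruited when the article was written, the change should be fixed and documented before any comparison by arm is seen.

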### Assessments during the follow-up phase

After completion of the study treatment, patients will be followed up every 3 months for the first 2 years and then every 6 months from the third year onward. All patients will be followed up until death or at least 3 years after treatment.

### Statistical analysis

Data analyses will be performed according to the intention-to-treat principle in all randomized patients. Between-group comparisons will be performed using chi-squared and Fisher’s exact test for categorical parameters and Student’s *t* test for normally distributed continuous variables or the Mann–Whitney *U* test or analysis of variance for nonnormally distributed continuous variables. Survival rates will be calculated using the Kaplan-Meier method, and comparisons between the groups will be performed using the log-rank test. The difference will be considered statistically significant at a *P* value of <0.05.

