## Methods

### Study design

This will be a prospective, two-arm, phase III randomized controlled trial aimed at assessing non-inferiority of dCCRT alone to consolidation chemotherapy following dCCRT in patients with locally advanced, inoperable ESCC. Each patient will be randomly assigned at a 1:1 ratio to receive either consolidation chemotherapy after dCCRT (Arm A) or dCCRT alone (Arm B; Fig. 1).

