### Sample size considerations

The sample size is based on data from a retrospective study [11] and a phase III randomized controlled trial [14]—which suggested that dCCRT yields 2-year OS rates of ≥60% and 56%, respectively. Therefore, we hypothesized that consolidation chemotherapy after dCCRT (Arm A) and dCCRT alone (Arm B) will yield 2-year OS rates of approximately 60% and 48%–65%, respectively. According to Power Analysis and Sample Size (version 15.0), these rates will be obtained with a two-sided type I error of 5% with 90% power, a type II error (β) of 20% with 15% noninferiority margin, and a dropout rate related to dCCRT or loss to follow-up of 5%. Therefore, the final sample size will be 600, with a 1:1 allocation in each arm.

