#### Chemotherapy interruption

Chemotherapy dose modifications will be based on the most severe toxicity in the patients' last cycle. In patients who develop grade 2 or higher hematological toxicity, chemotherapy will be delayed until the toxicity grade decreases to ≤1. At most, a 2-week delay will be permitted. Patients with a longer delay will be excluded from the trial and asked to discontinue chemotherapy.

Chemotherapy dose modifications may be required in the following situation: a patient develops grade 4 hematological toxicity or grade 3 or higher nonhematological toxicity, but the toxicity grade decreases to ≤1 within 2 weeks before the next cycle. Patients who remain ineligible after this period will be asked to discontinue chemotherapy.

If modification is necessary, cisplatin and capecitabine doses will be reduced to 75% of the planned dose. Dose modifications may be made at most twice; if more than two modifications are required, chemotherapy will be terminated.

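### Intention-to-treat is the only analysis set named for a non-inferiority claim; a per-protocol analysis and the consolidation receipt rate should stand beside it

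*Protocol article*

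**What the plan says.** The Study design section describes a trial "aimed at assessing non-inferiority of dCCRT alone to consolidation chemotherapy following dCCRT". The Statistical analysis section sets the population: "Data analyses will be performed according to the intention-to-treat principle in all randomized patients". It adds that "comparisons between the groups will be performed using the log-rank test", with significance at P < 0.05. The article mentions no per-protocol or as-treated set.

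Under Assessments during the treatment phase, patients without progression are randomized after dCCRT. (The interval given, two to six weeks, is read here as time since the end of dCCRT.) Under Chemotherapy, Arm A then receives two consolidation cycles and Arm B nothing further.

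Two sections foresee that treatment may not be delivered:

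- Exit criteria lists withdrawal on request, serious adverse events, and treatment not begun within four weeks of enrollment.
- Chemotherapy interruption ends chemotherapy, and participation in the trial, after a delay of more than two weeks.

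No expected rate of non-receipt is given. The 5% allowance under Sample size considerations is for dropout connected with dCCRT or for loss to follow-up.

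**The concern.** Consolidation is the only assigned difference after randomization. An Arm A patient who never starts it has been treated as in Arm B. Such patients can arise in one arm only, and if consolidation prolongs survival they shrink the observed difference. In a superiority trial that makes success harder to reach. Here it makes success easier.

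A finding of non-inferiority could then have two explanations: consolidation adds little, or too few Arm A patients received it. With only the intention-to-treat result, the reader cannot tell these apart. The difference matters because the Study objectives section frames the main question as survival in patients treated with or without consolidation, and a positive result would be used to argue for omitting it.

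**Working it through.** **The plan's own figure.** The article gives no figure on this point. Its sample size of 600 serves only as an input. For the record, 600 does not follow from equal 2-year rates of 60%, a 15-point margin and one-sided 2.5%:

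- 90% power: (1.960 + 1.282)² × (0.24 + 0.24) / 0.15² gives 225 per arm; 450 / 0.95 = 474 in total.
- 80% power: the same formula gives 168 per arm; 336 / 0.95 = 354 in total.

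That mismatch is a separate matter, as is the article's pairing of 90% power with a type II error of 20%.

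**Inputs from Sample size considerations**

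- 600 patients at 1:1, less 5%: 600 × 0.95 / 2 = 285 per arm.
- Error level: "a two-sided type I error of 5% with 90% power", hence one-sided 2.5% for non-inferiority.
- Margin: "a type II error (β) of 20% with 15% noninferiority margin".
- Anticipated survival: the arms "will yield 2-year OS rates of approximately 60% and 48%–65%, respectively".

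**Assumptions not in the documents**

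- The margin is in percentage points of 2-year survival.
- Non-inferiority is declared when the upper limit of the two-sided 95% interval for A minus B lies below 0.15. The article states only a log-rank test.
- The true rates are 60% with consolidation and 45% without, so the deficit equals the margin.
- A share f of Arm A receives no consolidation, has Arm B's survival, and does not otherwise differ in prognosis.

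**Formula.** The intention-to-treat difference is d = 0.15 × (1 − f), and Arm A's rate is pA = 0.45 + d. Then SE = √[pA(1 − pA)/285 + 0.45 × 0.55/285], and the probability of declaring non-inferiority is Φ((0.15 − d)/SE − 1.960).

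| f | d | pA | SE | (0.15 − d)/SE − 1.960 | Probability |
|---|---|---|---|---|---|
| 0% | 0.150 | 0.600 | 0.0414 | −1.960 | 2.5% |
| 10% | 0.135 | 0.585 | 0.0415 | −1.598 | 5.5% |
| 20% | 0.120 | 0.570 | 0.0416 | −1.238 | 10.8% |

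Simulation with 400,000 runs per row gives 2.5%, 5.4% and 10.7%. With 300 per arm the 10% and 20% rows become 5.6% and 11.1%.

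**Can 600 patients carry a per-protocol analysis?** Take both arms truly at 60%, with Arm A reduced to 285 × (1 − f) and Arm B at 285. Power is Φ(0.15/SE − 1.960).

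- Intention-to-treat: SE = √(0.24/285 + 0.24/285) = 0.0410; power 95.5%.
- Per-protocol, f = 10%: SE = √(0.24/256.5 + 0.24/285) = 0.0422; power 94.5%.
- Per-protocol, f = 20%: SE = √(0.24/228 + 0.24/285) = 0.0435; power 93.1%.

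Under the same assumptions the per-protocol contrast keeps the full 15-point deficit, so its false non-inferiority rate stays at 2.5%.

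**The case against.** The strongest reply is that intention-to-treat answers a legitimate question without bias: what follows from assigning consolidation or not. That stands. In the 10% row the true difference between the assigned policies is 13.5 points, inside the margin, so declaring non-inferiority is correct for that question. A reader might infer that the nominal 2.5% error simply fails. The documents do not support this: they define no estimand, and the inflation exists only relative to the effect of consolidation actually given.

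A second reply is that supportive analysis sets are often left to a fuller protocol or analysis plan, which may already contain one. This too has force. The published sentence nevertheless covers the data analyses without qualification; if a per-protocol set exists, one sentence in the article resolves the point.

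A third concerns how much non-receipt to expect. Randomizing after dCCRT, and only patients without progression, means failures during dCCRT cannot dilute the contrast. The four-week exit rule counts from enrollment, and the text does not say whether that means registration or randomization. A long delay before the second consolidation cycle leaves a patient partly treated, which dilutes less than the model. Larger non-receipt rates would give larger errors, but nothing in the article supports assuming them.

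A reader might also point to the rule that "if more than two modifications are required, chemotherapy will be terminated" as a source of untreated Arm A patients. It is a poor example. There are four cycles in all, two of them consolidation, and changes depend on toxicity in the preceding cycle. A third change would therefore normally arise only before the fourth cycle, after one consolidation cycle has been given.

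Finally, a per-protocol set conditions on events after randomization and can introduce selection bias. That is why it should accompany intention-to-treat and not replace it.

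**Conclusion.** The point holds as a cheap improvement. Intention-to-treat is the right primary analysis, and nothing here shows it to be invalid. The weakness is that it is the only set named, in a design where non-receipt in one arm moves the result towards the conclusion sought. In the illustration, 10% non-receipt raises false non-inferiority about the treatment given from 2.5% to 5.5%, and 20% raises it to 10.8%. These figures depend on an assumed receipt rate, decision rule, margin scale and true survival, and on non-receipt unrelated to prognosis. They show the direction and possible scale of the problem and do not predict this trial's error rate.

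**What to change.** Keep intention-to-treat as primary, and state that randomized patients who stop or exit treatment are still followed for survival and counted. The wording under Exit criteria and Chemotherapy interruption that removes patients from the trial must be reconciled with an analysis of all randomized patients.

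Add a pre-specified per-protocol analysis of overall survival against the same margin:

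- **Set.** Arm A: at least one consolidation cycle started. Arm B: no off-protocol consolidation before progression.
- **Time origin.** Follow-up starts from a stated landmark after randomization, applied identically in both arms. Survival currently runs from the start of dCCRT, before randomization. Without a landmark, early deaths and progressions before a first consolidation cycle would drop out of Arm A only.
- **Adjustment.** The stratification factors (tumor location and stage) and status after dCCRT.
- **Reporting.** Show the result beside intention-to-treat with the proportion of Arm A who received consolidation, and interpret a non-inferiority result cautiously if the two disagree. Requiring both analyses to succeed is optional.

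The cost is one extra analysis, somewhat less precise (power of 94.5% at 10% and 93.1% at 20% non-receipt, against 95.5%) and open to selection bias that adjustment may not fully remove. No additional patients are needed under these assumptions. With 200 patients recruited at the time of writing, it could still be specified in advance.

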**Methods:**

This is a multicenter, prospective, open-label, phase-III randomized controlled trial comparing non-inferiority of dCCRT alone to consolidation chemotherapy following dCCRT. In total, 600 patients will be enrolled and randomly assigned in a 1:1 ratio to receive either consolidation chemotherapy after dCCRT (Arm A) or dCCRT alone (Arm B). Overall survival will be the primary endpoint, whereas progression-free survival, locoregional progression-free survival, distant metastasis-free survival, and treatment-related toxicity will be the secondary endpoints.

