Even though dCCRT remains the predominant treatment modality for esophageal cancer patients, high-level evidence regarding the use of consolidation chemotherapy for patients with ESCC is highly insufficient. To date, no prospective study has compared the outcomes of dCCRT with or without consolidation chemotherapy in patients with ESCC. Nevertheless, the current prospective randomized controlled trial will aid in understanding whether consolidation chemotherapy after dCCRT yields relatively superior benefits in patients with locally advanced, inoperable ESCC.

In conclusion, our study will be a multicenter, prospective, open-label, phase III randomized controlled trial to investigate the efficacy and safety of consolidation chemotherapy following dCCRT in patients with inoperable ESCC. The study will make valuable contributions to the evidence regarding the effects of consolidation chemotherapy for esophageal cancer in China.

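### The trial asks a non-inferiority question, but the only test stated for overall survival is a log-rank test of no difference at P<0.05, which never uses the 15% margin

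*Protocol article*

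**What the plan says.** The Study design section describes a trial "aimed at assessing non-inferiority of dCCRT alone to consolidation chemotherapy following dCCRT", and the Methods part of the Abstract states the same aim. The Abstract adds that "Overall survival will be the primary endpoint".

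Sample size considerations gives a "two-sided type I error of 5% with 90% power" and then "a type II error (β) of 20% with 15% noninferiority margin". The margin stands beside expected 2-year survival of about 60% in Arm A and 48% to 65% in Arm B. The text does not say whether 15% is an absolute difference, a relative difference or something else.

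Statistical analysis names one analysis for survival: rates are estimated by Kaplan-Meier, and "comparisons between the groups will be performed using the log-rank test". The criterion that follows is "The difference will be considered statistically significant at a" P value below 0.05. The section contains no margin, no confidence-interval rule and no statement of what result would establish non-inferiority.

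Study objectives says only that overall survival will be compared. The end of the Discussion describes the trial as an aid to "understanding whether consolidation chemotherapy after dCCRT yields relatively superior benefits", which is the language of superiority.

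**The concern.** A log-rank test at P<0.05 tests the null hypothesis that the two survival curves are equal. The design needs a test of the null hypothesis that Arm B is worse than Arm A by at least the margin. Failing to reject the first null is not evidence against the second: a non-significant P can come from similar arms or from too few deaths. Rejecting the first null in favour of Arm A does not settle the matter either, because Arm B can be significantly worse and still lie within the margin.

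The trial could support leaving out consolidation chemotherapy. That conclusion needs a rule with a controlled error rate, fixed before the data are seen, and the printed rule does not provide one.

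**Working it through.** **Inputs.** Arm A 2-year survival 60%, dropout 5%, total 600 allocated 1:1, margin 15%, two-sided 5% (Sample size considerations). Minimum follow-up 3 years (Assessments during the follow-up phase). 200 recruited so far (Funding and current status). Evaluable per arm: 600 × 0.95 / 2 = 285.

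**Assumptions.** The margin is 15 absolute points at 2 years. True equality means 60% in both arms. Survival is exponential where hazard ratios and deaths are used.

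**0. The plan's own figure.** For equal 60% rates, n per arm = (z_α + z_β)² × 0.48 / 0.15². At one-sided 2.5% and 90% power this is 10.51 × 21.33 = 225 per arm, or 450 in total and 474 after 5% dropout. At 80% power it is 7.85 × 21.33 = 168 per arm, or 336 and 354. The stated 600 does not follow from these inputs, but nothing below depends on how it was reached.

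**1. The stated test at true equality.** It is significant 5% of the time by construction, 2.5% in each direction. Only the 2.5% favouring Arm B would imply non-inferiority.

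**2. A margin test at true equality.**
- SE = √((0.24 + 0.24)/285) = 0.0410.
- Power = Φ(0.15/0.0410 − 1.96) = Φ(1.695) = 0.955.
- Hazard-ratio check: the margin is ln 0.45 / ln 0.60 = 1.563. Three-year survival is 0.60^1.5 = 0.465, so deaths ≈ 570 × 0.535 = 305 and SE(log HR) ≈ 2/√305 = 0.1145. Power = Φ(0.447/0.1145 − 1.96) ≈ 0.974.

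**3. The two rules on one scale.** The 95% half-width for the 2-year difference is 1.96 × 0.0410 = 8.0 points. The margin rule needs an observed deficit below about 15 − 8.0 = 7.0 points, while a 2-year z-test stays non-significant up to about 8.0. A deficit between 7 and 8 points would be non-significant and would still fail the margin.

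**4. Error if P>0.05 were read as non-inferiority, with Arm B exactly at the margin (45%).**
- 2-year rate z-test: SE = √((0.24 + 0.2475)/n), error = Φ(1.96 − 0.15/SE).
- Log-rank with 3 years of follow-up: deaths = n × (0.535 + 0.698), SE = 2/√deaths, error = Φ(1.96 − 0.447/SE).

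| Per arm | z-test SE | z-test error | Deaths | Log-rank SE | Log-rank error | Margin test |
|---|---|---|---|---|---|---|
| 285 | 0.0414 | 4.8% | 352 | 0.107 | 1.3% | 2.5% |
| 100 | 0.0698 | 42.5% | 123 | 0.180 | 30% | 2.5% |

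The log-rank column corresponds to the test the plan names. The z-test column shows the same misreading applied to the 2-year rates beside which the margin is set.

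**5. The reverse conflict.** With Arm B truly at 51% (HR 1.32) and 570 patients, there is about a 6% chance of a log-rank result significantly against Arm B while the upper hazard-ratio limit is still below 1.563.

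**The case against.** The strongest reply is that this is a short, generic paragraph in a condensed article, and that an analysis plan not shown may hold the margin-based rule. That limits what can be said about how the trial will be analysed. It does not remove the mismatch in print: the section defers to no other document, and it states a test and a criterion that fit a different hypothesis from the one the design declares.

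Several stronger readings are tempting and should be resisted.

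- A reader might infer that the investigators will treat P>0.05 as non-inferiority. The article does not say so. The error rates in step 4 are conditional on that reading.
- A reader might conclude that the plan cannot answer its question at all. A log-rank result significantly favouring Arm B would imply non-inferiority. The chance is 2.5% at equality and about 30% if Arm B is at 65%, the top of the stated range.
- A reader might count non-significant results at true deficits of 10 or 12 points as false claims. Those deficits lie inside a 15-point margin, so they are not.
- A reader might take 30% to 43% as this trial's error. Recruitment continues towards 600 and no analysis at 200 is planned. Nor does the article say whether the 200 recruited have been randomised, which happens only after dCCRT. At the planned size the figure is 1% to 5%, on either side of 2.5%.

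The superiority wording in the Discussion is closing prose and carries less weight than the design statements, which consistently say non-inferiority.

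**Conclusion.** The point holds as a mismatch between hypothesis and stated test. The design and sample-size sections set a non-inferiority question with a 15% margin; the analysis section states a test of no difference that ignores it. Followed as written at true equality, the rule gives no verdict on the trial's question about 95% of the time, where a margin test on the same patients would succeed about 95% of the time. The two figures are close by coincidence.

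The existence of the mismatch rests on the text alone. Its size rests on 60% survival in both arms (the document gives a range for Arm B), an absolute 15-point margin, 285 evaluable per arm and, for the log-rank and hazard-ratio figures, exponential survival with proportional hazards. At full enrolment the case is not that the error would be grossly inflated. It is that the error is not fixed by the rule and would rise if the trial closed small. This should be corrected before the final analysis.

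**What to change.** In Statistical analysis, replace the survival-comparison sentence for the primary endpoint with one rule:

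- The primary analysis estimates the difference in Kaplan-Meier 2-year overall survival, Arm B minus Arm A, with a two-sided 95% confidence interval, stratified by the randomisation factors (tumour location and stage).
- Non-inferiority is declared only if the lower limit lies above minus 15 percentage points.
- Superiority is tested, by log-rank, only after non-inferiority is shown. The log-rank test also stays for the secondary time-to-event endpoints.
- A stratified Cox hazard ratio may be reported as supportive only. It is not interchangeable with the rate difference, because its matching margin of about 1.56 holds only under proportional hazards; offering both as primary would leave the test unfixed.

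In Sample size considerations, confirm that the 15% margin is an absolute difference in 2-year overall survival. In the Discussion, align the closing statement of aim with non-inferiority.

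The cost is wording in the protocol and analysis plan. No patients, visits or procedures change, and the article reports that recruitment is still open, so the rule can be set before the final analysis.
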